#### Withdrawal Criteria

An allergic reaction that is clearly associated with the study drug;Adverse symptoms or signs and abnormal examination results occur that are clearly related to intake of the study drug;Women who develop pregnancy during the study;Subjects request to withdraw from the study;Signs of severe or frequent hypoglycemia: hypoglycemic events that require help from others (e.g., increased physical activity or no meals), or weekly hypoglycemic events [plasma or hand-pricked blood glucose measurements ≤ 70 mg/dL ( ≤ 3.9 mmol/L); any episode with or without symptoms] occurring more than three times. Cardiovascular or cerebrovascular events that occur during the study including acute myocardial infarction, stroke, hospitalization for heart failure, etc.

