### Intervention

#### Treatment

Study group: general lifestyle intervention + Jinlida granules (three times a day at a dosage of 6 g each time) drug consumed with boiled warm water;

Control group: general lifestyle intervention + placebo (three times a day at a dosage of 6 g each time); drug consumed with boiled warm water;

The research drugs are recommended to taken after meals. If the patient has an intolerable adverse event that considered as relevant to the study drug based on the investigator's consideration, the patient should discontinue the medication. Treatment duration is at least 2 years.

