### Sample Size Calculation

According to “Lian et al. (23),” after 1 year of follow-up, the average annual incidence of diabetes in the placebo group was 29.32%. “Gao et al. (24)” demonstrated a cumulative incidence of diabetes in placebo group after 3 years of follow-up was 43.86%.

Our hypothesis assumes that the incidence of diabetes in the control group would be 40.0% after 2 years of intervention and the HR would be expected to be 0.75—the study drug is predicted to reduce the risk by 25%—employing α = 0.05, β = 0.20. The study group and the control group will be allocated in a 1:1 ratio. The study period will last 4 years, including 2 years of medication treatment and 2 years of follow-up. PASS16 software will be employed to calculate the sample size, each group should contain 395 subjects. Considering a 10% the violation rate and issues of inter-center case allocation, a total of 880 cases and evaluation of number of endpoint events 209:171 will be required to reach statistical significance.

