#### Statistical Analysis Method

□ All statistical tests will be performed using a two-sided test, and a *p* <0.05 (two-sided test) will be considered to be statistically significant results (except for special instructions).□ Descriptive analysis: This data is described by the number of cases and the composition ratio. The measurement data are described by means of mean, standard deviation, maximum value, and minimum value. The non-normal distribution data are described by median, 25th and 75th quantiles. A comparison between the two groups of general conditions will be based on outcomes. Quantitative data will be compared between groups using group *t*-test or Wilcoxon rank sum test, classification data using chi-square test, or exact probability method, grade data used Wilcoxon rank sum test, or CMH test, as appropriate.

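### Withdrawal Criteria and Treatment do not separate stopping the drug from leaving the study; read naturally, the former ends diabetes ascertainment for subjects whose withdrawal may relate to arm and to risk

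*Protocol article*

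**What the plan says.** The Withdrawal Criteria stand beside the inclusion and exclusion criteria. Among the triggers are "Adverse symptoms or signs and abnormal examination results occur that are clearly related to intake of the study drug" and "Cardiovascular or cerebrovascular events that occur during the study including acute myocardial infarction, stroke, hospitalization for heart failure, etc", along with drug-related allergy, pregnancy and severe or frequent hypoglycaemia. Only one item, the subject's own request, names what is being left, and it names the study. The other items give no object.

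The Treatment section covers an intolerable adverse event that the investigator considers drug-related. There, "the patient should discontinue the medication"; nothing is said about leaving the study.

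The primary outcome is the incidence of type 2 diabetes. Table 1 schedules an OGTT every three months in year 1, repeats the pattern to month 48, and adds a visit when an end event occurs. It has no column for subjects who have stopped the drug or been withdrawn. Intervention Cycles and Sample Size Calculation mention two years of follow-up, but tie it to neither group. The full analysis set definition does not mention outcomes after withdrawal, and the per-protocol set requires primary outcome data.

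**The concern.** A drug-related adverse event can fall under both sections, which give it different consequences. Investigators at 22 centres could apply them differently.

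On the natural reading of the withdrawal list, a subject who meets a trigger has no further OGTT, so a later diabetes diagnosis goes unrecorded. The triggers are not obviously neutral. Drug-related reactions and hypoglycaemia can differ in frequency between arms even under blinding. Subjects with a cardiovascular event may differ in metabolic risk from those without one. If withdrawal depends on arm and those withdrawn have a different diabetes hazard, censoring them makes it informative, and the subjects left under observation are no longer comparable as randomised.

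**Working it through.** **1. The plan's own figure.** Inputs from Sample Size Calculation: "employing α = 0.05, β = 0.20"; "the incidence of diabetes in the control group would be 40.0% after 2 years of intervention"; "the HR would be expected to be 0.75"; "The study group and the control group will be allocated in a 1:1 ratio"; four years in total. Two-sided testing is from Statistical Analysis Method ("All statistical tests will be performed using a two-sided test"), and two-year recruitment from Setting and Participants.

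- Events (Schoenfeld): 4(1.960 + 0.842)² / (ln 0.75)² = 379.4, so 380.
- Control hazard: λ = −ln(0.60)/2 = 0.2554 per year; study arm 0.75λ = 0.1916.
- Event probability with uniform accrual over 2 of 4 years: 1 − (e^(−2λ) − e^(−4λ))/(2λ) = 0.530 for control and 0.434 for the study arm.
- Per arm: 380 / (0.530 + 0.434) = 394.3, so 395. Events: 209.4 and 171.3, matching 209:171.
- Allowance: 790 / 0.90 = 877.8, so 878, rounded to 880.

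The stated sample size reproduces and is not affected by this point. The 10% allowance restores numbers. It does not protect against selective loss.

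**2. How the bias arises.** Assume no true effect. A subgroup of fraction x in each arm has hazard rλ, with the remainder scaled so that the arm average is λ at the start. In one arm the subgroup is withdrawn at month 6; in the other it stays. The hazard of those still observed in the first arm is then (1 − xr)/(1 − x) × λ. With x = 10%:

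- r = 2: (1 − 0.20)/0.90 = 0.889λ, so that arm looks better.
- r = 1: λ, no bias.
- r = 0.5: (1 − 0.05)/0.90 = 1.056λ, so that arm looks worse.

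The overall hazard ratio lies nearer 1 when r is 2, because the arms do not differ in the first six months and the high-risk subgroup retained in the other arm is gradually used up.

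**3. Simulated size.** 440 per arm, 10,000 trials per row, follow-up uniform on 2 to 4 years, withdrawn subjects censored at month 6, two-sided log-rank test at 5%. The log-rank test is an assumption in keeping with the hazard-ratio design. The first arm named is control.

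| Withdrawn, control vs study | Relative hazard r | Apparent HR | Type I error |
|---|---|---|---|
| 0% vs 2% | 2 | 0.99 | 5% |
| 0% vs 5% | 2 | 0.97 | 6% |
| 0% vs 10% | 2 | 0.94 | 9% |
| 0% vs 10% | 1 | 1.00 | 5% |
| 0% vs 5% | 0.5 | 1.02 | 6% |
| 0% vs 10% | 0.5 | 1.05 | 9% |
| 2% vs 5% | 2 | 0.98 | 5% |
| 5% vs 5% | 2 | 1.00 | 5% |

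A separate run of the 0% vs 10%, r = 2 case with 4,000 trials gave 10%, so I read this as 9 to 10%.

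**4. A harsher variant.** If withdrawn subjects are left out altogether, the observed risk is p/(1 − f + fr), where f is the fraction withdrawn and r here is a risk ratio. Take p = 209/440 = 0.475 in both arms, r = 2, and 2% vs 10% withdrawn. Control is 0.475/1.02 = 0.4657 and study 0.475/1.10 = 0.4318. The apparent HR is ln(1 − 0.4318)/ln(1 − 0.4657) = 0.90, with type I error 16.5%. At 2% vs 5% it is 0.96 and 6.8%. This describes an analysis restricted to subjects with a complete outcome, not one that keeps their time up to withdrawal.

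**The case against.** The strongest reply is that the document never says these subjects leave the study. Except for the subject's own request, the list names no object of withdrawal, and the Treatment section points to stopping the drug only. A reader might infer that subjects are definitely removed from the study and their outcome lost; the text does not establish that. This part of the reply stands.

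The article also condenses a fuller protocol, to which follow-up after stopping treatment is commonly left. Table 1 does not make its visits conditional on taking the drug. Silence alone would therefore be no finding. But the article is not merely silent: it prints a withdrawal list and a rule with a different consequence for an overlapping event. That conflict is in the text shown.

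A reader might further infer that the bias favours Jinlida. This needs withdrawn subjects to be at raised diabetes risk and to come mainly from the Jinlida arm. No section supports either. Placebo subjects can also be judged to have drug-related reactions under blinding, cardiovascular events occur in both arms, and subjects withdrawn for hypoglycaemia may well be at lower diabetes risk. The direction claim falls.

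Inflation of a crude chi-square test by unequal dropout is a separate question about the analysis method, not a consequence of these criteria, and is left out here.

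**Conclusion.** The point holds as an unresolved conflict in the printed text. Withdrawal Criteria and Treatment do not distinguish stopping the drug from leaving the study, and the natural reading of the former ends diabetes ascertainment selectively. It does not show that the randomised comparison is broken.

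With 10% of one arm censored at month 6, the apparent HR under no true effect ranges from about 0.94 to 1.05 for relative hazards of 2 to 0.5, with type I error up to about 10%. At 2% to 5% withdrawn, or with balanced withdrawal, the bias is slight or nil. The withdrawal fractions, their timing and the relative hazards are all assumptions; the document gives none of them. The change should be made because the protection is cheap and the size of the bias could not be established afterwards from data that were never collected.

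**What to change.** Leave every medical trigger as it stands. Reconcile Withdrawal Criteria with Treatment so that each trigger has one clear consequence: stopping the drug, leaving the study, or both. Which consequence applies is for the investigators to decide. Then add that, unless a subject withdraws consent for follow-up, diabetes ascertainment continues on the existing OGTT schedule to the planned end, and that the subject is analysed in the arm to which he or she was randomised.

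The cost is protocol wording and visits that Table 1 already schedules. The downside is that follow-up off the drug may dilute the estimated effect slightly.

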### Intervention

#### Treatment

Study group: general lifestyle intervention + Jinlida granules (three times a day at a dosage of 6 g each time) drug consumed with boiled warm water;

Control group: general lifestyle intervention + placebo (three times a day at a dosage of 6 g each time); drug consumed with boiled warm water;

The research drugs are recommended to taken after meals. If the patient has an intolerable adverse event that considered as relevant to the study drug based on the investigator's consideration, the patient should discontinue the medication. Treatment duration is at least 2 years.

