## Abstract

**Background:** Metabolic syndrome (MS) is a powerful risk factor for cardiovascular and cerebrovascular diseases. Although lifestyle intervention reduces several of the symptoms of the syndrome and cardiovascular risks, the lifestyle intervention that yields the benefits is restrictive. Jinlida is a Chinese patent medicine that has shown activity in type 2 diabetes, which has been approved in China. Preclinical studies in Jinlida granules support an improved role of abnormal glucose and lipids metabolism as well as reducing weight. Here, we describe the protocol of an ongoing clinical trial investigating a new therapy for metabolic syndrome in patients with abnormal glucose metabolism.

**Methods:** This study will enroll 880 subjects (aged 18–70 years) who have metabolic syndromes with abnormal glucose metabolism. All the participants in a double-blind, parallel, randomized, placebo-controlled trial, will receive Jinlida or placebo, orally, 9 g/time, three times daily for 2–4 years period on the basis of lifestyle intervention. The primary outcome measure (Incidence of type 2 diabetes) will be assessed during intervention cycles. Adverse events were monitored. All statistical tests will be performed using a two-sided test, and a *p* ≤ 0.05 (two-sided test) will be considered to be statistically significant results.

**Discussion:** Results from this study will provide evidence on whether incorporating oral Jinlida granules treatment into lifestyle intervention can delay or inhibit the development of diabetes mellitus in metabolic syndrome subjects with abnormal glucose metabolism.

**Clinical trial registration:** Registered at http://www.chictr.org.cn/enIndex.aspx. Trial registration number: ChiCTR1900023241.

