### Intervention Cycles

Eligible subjects will be randomly assigned to receive general lifestyle intervention + Jinlida granules at a dose of 9 g or general lifestyle intervention + placebo, orally, three times daily. The run-in period is 1 month, and the intervention will last 24–48 months. Follow-up will last 24 months.

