#### Analysis Subjects

The research subjects will be divided into the following categories:

1. Full Analysis Set (FAS)□ FAS refers to the data set obtained from all randomized subjects with the least amount and reasonable method of eliminating subjects. Exclusions usually include violations of important inclusion criteria; subjects do not receive treatment with the test medication; no observational data is obtained after randomization.2. Per Protocol Set (PPS)□ PPS is a subset of the full analysis set, and these subjects are more compliant with the trial. Subjects included in the PPS generally have the following characteristics: (1) the minimum exposure of the research drug in advance-completion, that is, the compliance with the drug is 80%; (2) the data of the primary outcomes in the test are available; (3) no major violation of the protocol.3. Security data set (Safety Set, SS)□ SS is a subject who received at least one-time treatment after randomization and has a safety assessment.

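### The article gives the dose as 6 g three times daily in one section and 9 g three times daily in two others, so a reader cannot tell which regimen the results will describe

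*Protocol article*

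**What the plan says.** Three places in the protocol article state an amount per intake.

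- **Abstract (Methods):** participants "will receive Jinlida or placebo, orally, 9 g/time, three times daily". One amount covers both arms.
- **Intervention, Treatment:** the study group takes "Jinlida granules (three times a day at a dosage of 6 g each time", and the control group takes "placebo (three times a day at a dosage of 6 g each time". Again the amount is the same in both arms, but it is a different figure.
- **Intervention Cycles:** subjects are assigned to "Jinlida granules at a dose of 9 g or general lifestyle intervention + placebo, orally, three times daily". The 9 g is attached to Jinlida; no separate gram amount is given for placebo.

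Two other statements depend on the regimen without giving its size. Analysis Subjects lists, as a feature of the per protocol set (PPS), that "the compliance with the drug is 80" percent. Sample Size Calculation plans on a hazard ratio for the study drug: "the HR would be expected to be 0.75".

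**The concern.** All three statements describe the treatment given after randomization in the same trial, so they cannot all be correct. The amount of test product is part of the definition of the treatment. The planned hazard ratio, the diabetes incidence and the adverse event rates will all be read as results of a particular daily exposure over at least 2 years, and the article gives two candidates for it.

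At stake are interpretation and replication: which regimen the efficacy estimate belongs to, and which exposure the safety data cover. A possible secondary effect concerns the PPS. A compliance percentage needs a prescribed or dispensed amount as its base, so an unclear amount could, under some scoring rules, change who counts as compliant.

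**Working it through.** **1. Set the statements side by side.** Daily amount = amount per intake × 3 intakes.

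| Section | Jinlida | Placebo | Daily amount |
|---|---|---|---|
| Abstract | 9 g × 3 | 9 g × 3 | 27 g |
| Treatment | 6 g × 3 | 6 g × 3 | 18 g |
| Intervention Cycles | 9 g × 3 | no amount given | 27 g (Jinlida) |

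Ratio: 27 / 18 = 1.5. Equivalently, the lower figure is 1 − 18/27 = 33% below the higher.

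**2. Look for an explanation in the text.** No section describes a titration, a dose reduction, a second dose level or an amended dose, and no other section states an amount. The Randomization and Blinding sections describe numbering, packaging and dispensing but give no grams. Both figures belong to the current text, so this is not a difference from superseded wording.

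**3. See whether the text ranks the figures.** It does not. The 9 g appears in two separate sections. The 6 g appears once for each arm in the section that defines the intervention. Neither a count of mentions nor the standing of a section settles the matter.

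**4. Work through the PPS criterion.** The 80% limit in grams is:

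- 0.80 × 18 = 14.4 g/day
- 0.80 × 27 = 21.6 g/day

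What follows depends on how compliance is scored, which the article does not say.

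- *Against the drug dispensed:* compliance = (dispensed − returned) / dispensed. The amount per intake cancels, and a subject who takes everything is 100% compliant at either figure.
- *In grams, against the same figure as dispensed:* again 100%.
- *In grams, dispensed at 18 g/day but scored against 27 g/day:* 18 / 27 = 66.7%, so a fully adherent subject falls below 80%.
- *The reverse mismatch:* a subject dispensed 27 g/day who takes 14.4 g/day has used 14.4 / 27 = 53.3% of the drug, yet would pass, since 14.4 / 18 = 80%.

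PPS membership is thus affected only under the last two rules, where dispensing and scoring use different figures.

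**5. Check whether the sample size depends on the dose.** It does not. Events = 4(1.960 + 0.842)² / (ln 0.75)² = 31.4 / 0.0828, about 380. The article's 209 and 171 also sum to 380. With 40% incidence at 2 years, exponential event times, 2 years of uniform accrual (assumed) and 4 years in total, the event probabilities are 0.530 and 0.434. This gives 380 / (0.530 + 0.434), about 394 per group against the stated 395. No gram amount enters.

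**The case against.** The strongest reply is that this is a reporting slip in a journal article and no more. Enrollment began in August 2019, so an operational protocol and packaged drug already existed when the article was written. Condensation does excuse omissions. It does not excuse two incompatible statements of one fact, so the contradiction stands.

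Three stronger readings are tempting, and the reply is right about each.

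- **A reader might infer that the trial itself has no fixed regimen.** The article shows only that the dose is reported inconsistently. The full protocol is not at hand, and one error in the article would produce the same text.
- **A reader might infer that sites following different sections gave different amounts within one arm.** Nothing supports this. According to Randomization and Blinding, drug is packaged and numbered in advance by blinding personnel and dispensed by drug number through a central system, with the treatment plan held consistent across packages. Error is not excluded, because label instructions are not shown, but mixed dosing is speculation.
- **A reader might infer that a subject taking all of 18 g/day is dropped from the PPS as 67% compliant.** Analysis Subjects does not say that compliance is counted in grams. Table 1 schedules both distribution and recovery of drug, which allows scoring against what was dispensed. The 67% arises only if drug is dispensed under one figure and scored under the other.

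Nor is the comparison between arms shown to be harmed: the two sections that give an amount for both arms give the same amount to each.

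**Conclusion.** The inconsistency is real and is wrong as written: 18 g/day in one section, and 27 g/day in two others (in one of these for Jinlida only). That is a factor of 1.5 in the daily amount of the test product, with no explanation in the text. The consequence that can be supported is that a reader cannot determine which regimen and exposure the efficacy and safety results describe. An effect on PPS membership is conditional on compliance being scored in grams against a figure other than the one dispensed.

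This conclusion rests on the article alone and assumes that all three sections refer to the same treatment period, which their wording supports. It does not rest on any view of which figure is correct; the documents do not show that. It is not evidence of a fault in conduct, randomization, blinding or sample size. It should nevertheless be corrected, because the dose defines the treatment under test.

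**What to change.** The sponsor should reconcile the Abstract, Treatment and Intervention Cycles sections against the approved protocol, the drug labels and the packaging records. It should then:

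1. State one regimen, for both arms, in all three places, including the placebo amount that Intervention Cycles leaves out.
2. Base the compliance calculation for the PPS on that regimen.
3. Check that the registry entry agrees. The entry is not visible here, so this is a check and does not presume an error there.
4. Only if the records show that both amounts were dispensed, report the split by arm.

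No dose is proposed here. The cost is an erratum to the article, a check of labels and packaging records, and a look at the registry entry. Neither the sample size nor the randomization needs to change.

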#### General Lifestyle Intervention

The Guidelines for the prevention and treatment of type 2 diabetes (2017 edition) (3) suggest that subjects with abnormal glucose metabolism should reduce their risk of diabetes through diet control and exercise. Regular follow-up and psychosocial support to ensure that lifestyle changes can persist for a long time are needed; as well as checking blood glucose regularly and paying close attention to other cardiovascular risk factors (such as smoking, hypertension, dyslipidemia, etc.) including giving appropriate intervention measures. The primary objectives of the intervention are as follows:

Maintaining a healthy weight: the weight loss goal for overweight/obese subjects is 5–10% of weight loss in 3–6 months. A lean patient should maintain an ideal body weight through a reasonable nutrition plan.Providing a balanced diet to meet the physical demand for micronutrients.Achieving and maintaining ideal blood glucose levels as well as reducing HbA1c levels.Reducing risk factors for cardiovascular disease including control of dyslipidemia and high blood pressure.

In addition, dietary and exercise intervention as well as smoking cessation are important in demonstrating the value of metabolic syndrome control. All recommendations were recommended by the guidelines (3) and related details are also uploaded to the Supplementary Material.

Emphatically, in this study, most subjects come from the communities and hospitals. We designate the community workers or medical stafvies to manage the patients for lifestyle intervention and keeping detailed records in the designed form, in order to maintain two groups in balance.

